## Methods

### Design

We registered this single-blind randomised clinical trial in 2013 (identifier NCT01783457). Patients with a first episode of psychosis between 2010 and 2014 are to be included and randomly assigned to one of two treatment groups: the control group, receiving pharmacotherapy together with regular sessions with a psychiatrist (treatment as usual), and the intervention group receiving integrated treatment, namely treatment as usual plus a psychoeducational intervention (12 main sessions and 2 booster sessions). A first psychotic episode was defined as the first time a patient displayed positive psychotic symptoms of delusions and/or hallucinations.

We are recruiting patients from five psychiatric centres (University Hospital of Álava, Clinic Hospital of Barcelona, Clinical Foundation of Valencia, University Hospital of Bellvitge, and University of Valencia) that agreed to take part in the e-learning project. In all centres, the clinicians recruit subjects who show psychotic symptoms for the first time, and who meet the inclusion criteria (listed below). To obtain 90% power to detect differences in the means at the 5% level of significance, we have estimated that we need to enrol 130 patients in each group (study group and controls) (alpha = 0.05; beta = 0.10; n = 260).

The treatment is being supervised by one clinician (PV) trained by a highly experienced clinician at the University Hospital of Álava (SB), while the evaluations in all centres are conducted by other clinicians blind to patient allocation.

#### Inclusion criteria

For patients to be included, they must have experienced a first episode of psychosis. All those included must have met *Diagnostic and Statistical Manual of Mental Disorders* 4^th^ edition text revised (DSM-IV-TR) criteria for one of the following within the previous 5 years: schizophreniform disorder, schizoaffective disorder, brief psychotic disorder, delusional disorder, non-specified psychotic disorder, bipolar disorder with psychotic symptoms, or major depressive disorder with psychotic symptoms. In addition to giving informed consent, they must also be between 18 and 45 years old and speak good Spanish.

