#### Exclusion criteria

Subjects with mental retardation, organic brain disorders or the presence of any comorbid condition that could hinder communication, or drug abuse as a primary diagnosis, were excluded.

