## Discussion

The project we describe in this paper represents an innovation in our setting given that it uses an online training platform, in which supervision, training and question and answer sessions are carried out remotely, facilitating access by all professionals, and reducing financial and time costs.

On the other hand, the integrated treatment itself is based on strategies that have proven to be effective, and, depending on the results, this project might lead to its adoption in routine practice in our setting. In addition, the close monitoring of first episodes of psychosis associated with the study provides extra data, improving our knowledge and understanding of the situation of these patients and, in turn, allowing treatments to be optimised. Finally, the proposed intervention at the onset of the disease will enable the patients to reap the benefits of early intervention, not only at the pharmacological level, but also in the areas addressed by adjunctive treatments that have proven to be effective [48], but that are not currently in the portfolio of services offered in our health centres.

With regards to the limitations of this study, first of all some variables are measured by self-report and patients could under- or overestimated their symptoms, but patients are also assessed by clinicians. Further, although the scales employed are among the most widely used by clinicians and researchers in this type of patient, results may not be comparable between studies if different instruments are used. Finally, although we have already recruited many patients and recruitment continues to the end of 2014, the power of the study would be increased with a larger sample size and, to assess the longer-term impact of the intervention, a longer monitoring period should be considered (>6 months). On the other hand, this is the first study in our setting assessing this type of therapy and this type of innovative training with a rigorous methodology (structure and content).

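### Design, Inclusion criteria and Discussion describe different populations, so time since onset and current symptom status at entry are not fixed

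*Protocol article*

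**What the plan says.** The Design section of the protocol article gives a strict definition: "A first psychotic episode was defined as the first time a patient displayed positive psychotic symptoms of delusions and/or hallucinations". It then says that "the clinicians recruit subjects who show psychotic symptoms for the first time, and who meet the inclusion criteria (listed below". Its calendar statement reads "Patients with a first episode of psychosis between 2010 and 2014 are to be included"; the years could date either the episode or the enrolment.

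The Inclusion criteria are looser. Patients qualify if "they must have experienced a first episode of psychosis" and if they met DSM-IV-TR "criteria for one of the following within the previous 5 years". The diagnoses listed are all psychotic disorders or mood disorders with psychotic symptoms. Age, language and consent are the only other conditions. The Exclusion criteria begin "Subjects with mental retardation, organic brain disorders or the presence of any comorbid condition that could hinder communication" and add primary drug abuse. They say nothing on remission, symptom level, time since onset or earlier relapse.

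The Discussion states that "the proposed intervention at the onset of the disease will enable the patients to reap the benefits of early intervention".

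**The concern.** The Inclusion criteria put the first episode in the past and allow up to five years since the diagnostic criteria were met. The Design section puts it in the present. A centre screening from the criteria list and a centre screening from the Design text could enrol different patients, and five centres are recruiting.

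Two things are at stake.

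- **Sensitivity of the primary comparison.** The primary objective is improvement on PANSS, STAI and HRSD. Each of the 30 PANSS items is scored from 1, so the total cannot fall below 30. A patient in remission at entry has little room to improve on that scale.
- **What the result can be said to show.** A statement about treating at onset does not describe a patient who enters years after a first episode. The recurrence-free analysis would also pool patients in their first episode with any who have already relapsed, and the Background itself says that recurrence is the usual course.

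**Working it through.** **Step 1: set the sections side by side.** Take three hypothetical adults who meet the age, language and consent conditions.

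| Patient at screening | Inclusion and Exclusion criteria | Design, recruitment sentence | Discussion, onset wording |
|---|---|---|---|
| First-ever delusions now, listed diagnosis made now | Eligible | Fits | Fits |
| Listed diagnosis four years ago, now remitted | Eligible | Does not fit | Does not fit |
| First episode two years ago, now relapsed | Eligible | Does not fit | Does not fit |

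The second and third patients pass the criteria list and fail the recruitment sentence.

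**Step 2: ask whether the calendar sentence settles it.** If 2010 to 2014 dates enrolment, it says nothing about time since onset. If it dates the episode, an episode early in 2010 with enrolment late in 2014 (the Discussion gives the end of 2014 as the close of recruitment) is still just under five years old. Neither reading limits entry to recent onset.

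**Step 3: ask what the five-year window does if both rules apply.** Someone displaying psychotic symptoms for the first time now could hardly have met a listed diagnosis years ago, since each one involves psychosis. So if the Design sentence governs, the window has almost no function. If the window has a function, the Design sentence misdescribes the sample.

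**Step 4: illustrate the possible loss of power.** The plan's figure of 130 per group cannot be reproduced forwards, because no difference or standard deviation is stated. It can be solved backwards.

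Inputs from the Design section: alpha 0.05, power 90%, 130 per group. Assumed: a two-sided test (sidedness is not stated) and the normal approximation.

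Implied standardised difference: d = (1.960 + 1.2816) × √(2/130) = 3.2415 × 0.12403 = 0.402. A one-sided test would give 0.363.

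Now assume that d applies to symptomatic patients, that a share f is remitted at entry, and that remitted patients keep a fraction k of the effect, with the standard deviation unchanged. The average effect is d × (1 − f(1 − k)), and

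power = Φ(3.2415 × (1 − f(1 − k)) − 1.960).

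For f = 25%:

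- k = 0: Φ(3.2415 × 0.75 − 1.960) = Φ(0.471) = 0.68
- k = 0.5: Φ(3.2415 × 0.875 − 1.960) = Φ(0.876) = 0.81

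| Assumed remitted share | Power, no effect in remitted | Power, half effect in remitted |
|---|---|---|
| 0% | 90% | 90% |
| 10% | 83% | 87% |
| 25% | 68% | 81% |
| 50% | 37% | 68% |

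The documents give neither f nor k, so the table shows a range and is not an estimate.

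**The case against.** The strongest reply is that the Design section joins the two rules with a conjunction: patients must show symptoms for the first time and also meet the listed criteria. The Randomisation section likewise speaks of first-episode patients who meet the selection criteria. On that reading the remitted patient is never eligible. This stands as far as it goes: the text does not establish that remitted patients are being enrolled. It does not remove the inconsistency, because the window is then nearly redundant and the criteria list, read alone, says something else.

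Breadth may also be deliberate. The Background calls the trial pragmatic and treats the first five years of illness as the critical period, and the programme includes relapse prevention and adherence, which suit patients past the acute phase. This also stands. A five-year window is consistent with that rationale, so a reader who infers that the early-intervention idea as a whole does not fit the sample goes too far. The conflict is with the narrower onset wording in the Discussion and with the recruitment sentence in Design.

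A reader might further infer that remitted patients do dilute the symptom effect. The documents do not support that as fact: they give no remitted share, no baseline severity and no effect by stage of illness. Remission of psychosis does not put anxiety or depression scores at their floor. Zero effect in remitted patients is the extreme case, and the unstated planning difference may already have been set for a mixed population, in which case there is no shortfall.

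Finally, a condensed article need not list every variable collected or every covariate. That time since first episode is not mentioned is therefore not itself a fault.

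**Conclusion.** The point holds as an inconsistency in the definition of the eligible population across Design, Inclusion criteria and Discussion. That part needs no assumption. Time since onset and current symptom status at entry are left open to each centre's reading.

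The consequence is conditional. If centres apply the Inclusion criteria alone, a mixed sample could lower the power of the symptom comparisons and would limit what can be said about onset. It would not bias the comparison between arms, which randomisation protects. The illustrative fall from 90% to between 68% and 81% at a 25% remitted share rests on a two-sided test, an implied difference of 0.402 that the article does not state, an assumed share, and an assumed effect of zero to one half in remitted patients. No actual loss of power is shown.

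**What to change.** 1. Reconcile Design, Inclusion criteria and Discussion into one statement of who is eligible, covering time since first episode and whether current symptoms are required, and make clear what the 2010 to 2014 range dates. Which clinical rule to adopt is for the trial team. Recruitment was still open at submission, so the statement can still guide the centres.
2. Derive time since first episode from the records for every patient, including those already enrolled.
3. In the analysis of covariance under Data processing, include the baseline value of each symptom score and time since first episode as covariates.
4. Report results by time since first episode as a supportive subgroup only. Restricting the main conclusion to recent-onset patients is not advised: any cut-point would be arbitrary, the group would be smaller, and the whole-sample randomised estimate would be set aside.
5. Word any conclusion about onset to match the patients actually enrolled.

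The cost is a wording amendment, one date per patient and slightly more analysis work. No new visits are needed.

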#### Exclusion criteria

Subjects with mental retardation, organic brain disorders or the presence of any comorbid condition that could hinder communication, or drug abuse as a primary diagnosis, were excluded.

#### Ethical considerations

The study is conducted in compliance with local regulations and internationally established principles of the Declaration of Helsinki (64^th^ World Medical Association General Assemble, Fortaleza, Brazil, 2013). The study and protocol were approved by the Clinical Research Ethics Committee of each participating health centre (University Hospital of Álava: HS/PI2010009: Clinic Hospital of Barcelona: 2010/5890, Clinical Foundation of Valencia; 2010/2904, University Hospital of Bellvitge: PR079/10, and University of Valencia: 2010/2904). Before inclusion, all patients are required to sign an informed consent form that includes a specific section covering genetic testing (for the BDNF analysis, see below).

#### Randomisation

All individuals with first episode psychosis that meet the selection criteria are randomised with random allocation software. For this purpose, all the groups from the participating centres send the initials of each patient recruited to researchers at the coordinating centre who specify the allocation of the patient (to the control or intervention group); the person in charge of the assessments is blind to this process.

#### Pharmacotherapy

For all participants, the pharmacological treatment used is that which patients have been prescribed by their psychiatrists, independent of their participation in the study.

### Patient assessment

Data are collected on the wide range of clinical and demographic variables detailed below and are entered on a data collection form. All the patients are assessed at baseline and have been or will be assessed at 6 months after inclusion in the study, which corresponds to the end of the psychoeducational programme in the case of the intervention group.

#### Demographic data

Data are collected on age, sex, level of education, living arrangements and employment status.

#### Symptomatology

Participants’ symptoms are assessed using the PANSS [23]. This instrument is composed of 30 items that assess positive and negative symptoms as well as the general psychopathology of the disorder. Each item is measured using a 7-point Likert scale reflecting the severity of symptoms, from 1 (none at all) to 7 (extreme symptoms). This scale has been validated in Castilian Spanish [24].

Trait and state anxiety are measured using the STAI [25]. This instrument has two parts: one assesses the anxiety experienced by patients in the previous week (state) using 20 items with four response options; while other part, also composed of 20 items with four response options, assesses their usual reactions to certain situations (trait anxiety). The STAI was adapted from the version described in a Spanish paper by Bermúdez in 1978 [26]; across all these items the mean and the reliability (Cronbach’s alpha and test-retest correlation) are similar to those of the original version [27].

Patients’ social anxiety is assessed using the LSAS [28], and its psychometric properties have been found to be satisfactory in the Spanish population [29]. Lastly, mood is evaluated using the HRSD [30], which has also been validated in Castilian Spanish [31].

In addition, in relation to symptoms, we record information on the number of relapses and hospital admissions (psychotic episodes) and the dates on which they occur for 2 years follow-up, the psychopharmacotherapy administered, family history of mental health problems, and record of substance use both before and after the intervention.

#### Patient awareness of their disease

Patient insight into their illness is measured using SUMD [32]. This scale provides broad assessment of patient thoughts and beliefs regarding their disease and medication. The Spanish adaptation of the SUMD is equivalent to the original version, and it has a similar reliability and external validity [33].

#### Prognosis

Prognosis is explored using the Strauss and Carpenter Prognostic Scale [34–36], an instrument that assesses the best status of the patient in the previous year in four areas: hospitalisations, work, social activity, and global functioning and, on the other hand, symptoms considering the previous month only. It is an interview-administered instrument with Likert-type response options ranging from 0 to 4, higher scores indicating a better prognosis. It has been validated in Castilian Spanish for schizophrenia [37].

#### Functioning

The overall function of patients is rated using a Spanish version of the GAF scale. This scale is recommended for Axis V in the multiaxial system of DSM-IV-TR [38] and is based on the opinion of clinicians regarding the level of general activity and functioning of patients. It has been validated in individuals with severe mental disorders [39].

Functional status is also assessed using FAST [40]. This is an interview-administered scale that assesses a patient’s functioning over the previous 2 weeks in six areas: autonomy, occupational functioning, cognitive functioning, financial issues, interpersonal relationships and leisure time. The FAST showed strong psychometric properties in Spanish individuals with first episode psychosis [41].

#### Treatment adherence

Adherence is estimated using the Morisky Medication Adherence Scale [42]. This instrument has been validated for the Spanish population [43]. It has four questions and assesses the attitudes of the patients towards their treatment. Patients with a score of 4 were considered to have ‘good’ adherence, while those with a score between 0 and 3 were classified as having ‘bad’ adherence.

#### Quality of life

The quality of life is measured using two instruments. First, the World Health Organization Quality of Life WHOQOL-BREF questionnaire [44] was used; this short version being composed of 26 items exploring four dimensions: physical health, psychological health, social relationships and the environment. Spanish field trials have confirmed that this questionnaire has adequate psychometric properties [45].

Second, the EuroQoL questionnaire [46] was used. The main part of this measures five dimensions (EQ-5D): mobility, self-care, usual activities, pain/discomfort and anxiety/depression. It also contains a visual analogue scale (EQ-VAS) represented by a vertical line on which subjects rate their self-perceived health status from 0 (the worst) to 100 (the best imaginable health status). The questionnaire is considered a simple, valid and practical measure and the Spanish version has been validated [47].

All the instruments used have demonstrated adequate psychometric properties and have been used in many other studies. Interviews are conducted by clinicians who have good inter-rater reliability for the scales used (PANSS, kappa = 0.80; STAI, kappa = 0.77; GAF, kappa = 0.95; LSAS, kappa = 0.83; HDRS-21, kappa 0.79; SUMD, Kappa = 0.81; Strauss–Carpenter, kappa = 0. 79; Morisky Medication Adherence Scale, Kappa = 0.94, FAST, Kappa = 0.88, WHOQOL-BREF, Kappa = 0.81 and Euroquol, Kappa = 0.78).

#### Biochemical analysis

To investigate BDNF in peripheral blood, blood samples are collected in the morning (on two occasions, like the other assessments, once at baseline and once at 6 months after inclusion). Plasma BDNF levels are measured using a BDNF Sandwich enzyme-linked immunosorbent assay kit (CYT306; EMD Millipore Corporation, Billerica, MA, USA), according to the manufacturer’s instructions. Blood cells are immediately separated from the plasma and processed. Standard curves are constructed using plasma duplicates. The absorption at 450 nm is measured with a Synergy HT microplate reader (BioTek Instruments, Winooski, VT, USA).

### Online training

The coordinating group carried out the training of the therapists in the participating centres, via teleconferencing (WebEx Training Center). The course consisted of 12 modules and 2 booster sessions, corresponding to the 14 sessions of the psychoeducational programme, and all the participating groups received the same theoretical content. Once all the materials had been provided and explained, participating groups were asked to perform a task with certain objectives, each group having to complete this before starting the following module.

In addition, all the therapists participating in the online training had to prepare a case study with theoretical and practical elements and correctly complete a task under the supervision of a psychotherapist with extensive experience in the field of psychoeducation, before they themselves carried out the psychoeducational intervention with the patients. As well as providing written support material, we attempted to ensure the correct integration of knowledge presented by giving feedback, correcting answers participants gave during sessions, and correcting hypothetical cases presented. At the end of each module, all the therapists were required to complete a form recording the learning objectives covered in the module and testing their knowledge of theoretical and practical aspects of the psychoeducation programme.

### Intervention programme

#### Integrated treatment

The psychoeducational programme has 14 1-hour sessions (12 main sessions and 2 booster sessions), fortnightly, for a period of 6 months, focused on improving patient insight into their illness, treatment adherence, prodromal identification, early intervention to prevent relapses, healthy lifestyles, techniques for managing anxiety, social skills and problem solving.

The programme includes the following sessions:What is a first episode of psychosis?The challenge and importance of insight into vulnerabilitySymptom recognitionPrevention of relapses: protective and risk factorsWhat can I do if I note the symptoms emerging again?Treatment adherenceHealthy lifestyles: sleep and sexualityHealthy lifestyles: substance useAnxiety management techniques (I)Anxiety management techniques (II)Social skills: assertiveness techniquesProblem-solving techniques

We have checked the completeness of the training with respect to the administration of the sessions both in terms of content and their structure. The psychoeducational sessions are run with the same interval between sessions in all the centres. Further, the therapists give the psychoeducational intervention to all patients in the same way and provide the same information, enhancing the reliability of the study.

If patients report any personal, social, work-related or family problems during the sessions, they are to be helped using cognitive behavioural techniques (psychotherapeutic intervention). Lastly, if patients have any question regarding what they are taught during the sessions, or about their condition, they can call a telephone helpline in working hours (between 08.00 and 15.00 from Monday to Friday). The aim of this service is to facilitate patient access to information and address any questions they might have.

